## **Study Protocol: Physiological Studies to Investigate the Effects of Kisspeptin on Human Brain Processing.**

### **Background**

Psychosexual dysfunction affects 1 in 3 people (1) with profound consequences for individuals and their partners, impairing quality of life and interpersonal relationships as well as reducing chances for successful conception (2). Psychosexual dysfunction is caused by problems with sexual functioning due to a psychological rather than a physical condition. It involves several disorders including impotence and reduced sexual desire. In the UK the cost of treating psychosexual disorders with medical and psychological therapy is estimated at £32 million/year (3). Current medical treatments are limited by side-effects such as increased heart disease and cancer risk (4), and engagement with psychological therapies continues to be poor. Therefore, there is an unmet need to understand human sexual brain processing to help develop safer and more effective treatments.

The limbic system is an area of the brain known to control memory, emotions and behaviour, including those related to sexual desire and reproduction. Kisspeptin is a hormone which activates the reproductive axis leading to onset of puberty and stimulation of LH pulsatility. Kisspeptin is also widely expressed in the human limbic system and associated brain areas (5,6). When given to healthy men, kisspeptin reduces sexual aversion and negative mood with specific brain changes seen on functional magnetic resonance imaging (fMRI) (7). In animals, kisspeptin action at its receptor is required for olfactory-mediated sexual behaviour i.e. when male mice lose their kisspeptin receptors, they also lose the ability to preferentially sniff out a female partner (8). Mood is an important factor in psychosexual dysfunction and our recent study showing diminished negative mood in healthy men receiving kisspeptin (7) is consistent with animal data demonstrating antidepressant-like effects and modulation of fear response by kisspeptin via the serotonergic system (9,10).

Furthermore, kisspeptin also excites nerve fibres in specific memory formation areas within the hippocampus and amygdala of the limbic system (11). Cognitive testing in mice shows that administration of kisspeptin directly into the brain enhances learning, object recognition and memory consolidation (12,13). In addition, kisspeptin is reported to prevent Amyloid— $\beta$  peptide neurotoxicity in vitro, which is the key mechanism for the development of Alzheimer's disease (14). Following on from these promising animal data, it is imperative to undertake human studies in order to assess whether kisspeptin has similar effects on human brain processing. Findings from these studies will deepen our understanding of human behaviour and cognitive processes with the aim of developing potential future therapies for psychosexual disorders and other conditions.

### **Objective**

This study is designed to investigate the physiological effect of the naturally-occurring hormone kisspeptin on human brain processing compared to placebo (vehicle) using functional magnetic resonance imaging (fMRI).

**Kisspeptin**

Kisspeptin is a naturally occurring hormone, which is known to play a critical physiological role in human fertility. Kisspeptin has been given safely to over 500 male and female participants in intravenous and subcutaneous form without side effects (15–18). The dose of kisspeptin administered in this study will not exceed 0.72nmol/kg/min. This dose has previously been demonstrated to safely produce a biological effect without untoward side effects (18). Similarly, the dose of intranasal kisspeptin will not exceed 0.72nmol/kg/min.

As per the MHRA algorithm, “Is it a clinical trial?”, the proposed study is not a clinical trial but rather an investigation of the physiological roles of kisspeptin and how it can modulate sexual and emotional brain processing in response to different stimuli. Vehicle administration will consist of gelofusine or normal saline. Kisspeptin and vehicle administration will not exceed 105 minutes duration.

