**Functional Brain MRI scan**

Magnetic resonance imaging (MRI) is a safe and established imaging technique, which has been used routinely in hospitals throughout the world for over 30 years. MRI does not involve the administration of radiation, and has no associated health risks. Functional MRI (fMRI) is a type of MRI that is used to determine which areas of the brain have greatest blood flow as a surrogate marker of brain function. fMRI uses blood oxygen level dependent (BOLD) analysis, which requires no contrast agent or drug administration. The MRI scanner contains a very strong magnetic field and individuals with any type of metal implanted in their body which could move in this field cannot undergo magnetic resonance imaging for safety reasons. This will be carefully checked for and such individuals excluded at the time of initial screening. MRI safety criteria will also be confirmed by MRI staff prior to each scan. In some circumstances, participants may attend for a pre-study acclimatisation visit during which they will undergo an anatomical brain MRI.

Participants will have the opportunity to watch a video about what to expect in the scanner at their screening visit. Participants lie supine in the scanner with their head placed in a padded head coil for support. At all times the participant will have access to an alarm button and will be able to verbally communicate with the investigator at the scanning console in-between scans. Maximum scan time per study visit will be 75 minutes, starting after administration of kisspeptin or vehicle. Participants will be able to communicate with the researchers throughout the scan and will receive reassurance as required.

All scans will be formally reported by a consultant neuroradiologist. Very rarely, abnormalities may be detected that warrant further investigation. In this situation the report would be communicated to the participant’s GP, who will arrange the appropriate specialist referral. A significant abnormality would lead to exclusion from further participation in the study.

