**Secondary Outcomes:**

- Changes in hormones such as luteinising hormone (LH), follicle-stimulating hormone (FSH), kisspeptin, oestradiol, testosterone, cortisol, and oxytocin during kisspeptin administration compared to vehicle.
- Changes in psychometric and behavioural parameters (including sexual, emotional and cognitive domains) during kisspeptin administration compared to vehicle.
- Correlation of changes in fMRI BOLD activity with psychometric and behavioural parameters during kisspeptin administration compared to vehicle.

**Study Design:** This project involves a randomised, two-way crossover placebo (vehicle) controlled study requiring 35 participants in each study group (A to F). Following their screening visit, suitable participants will attend for two fMRI study visits (one for kisspeptin and one for vehicle administration). Participants may also be invited to attend for two additional non-fMRI study visits (similarly one for kisspeptin and one for vehicle administration). Participants may consent for the two fMRI or two non-fMRI study visits or all four study visits. Each visit will last up to 4 hours to include preparation and post-study monitoring.

**Pre-Study Visits:** Participants will be asked to abstain from alcohol and caffeine from midnight before their study visits and to consume a normal breakfast on their study days. All study visits will start in the morning to ensure peak basal reproductive hormone levels. In addition, participants will be asked to abstain from sexual activity from midnight before their study visits, as sexual activity prior to the study can result in changes in testosterone levels and residual limbic brain activity (7).

**fMRI Study Visits:** Both study visits will take place at the Invicro Centre for Imaging Sciences and all participants (groups A to F) will receive the same protocol (see figure 1) during each study visit.

[figure not shown]

Kisspeptin will be administered during one study visit and vehicle will be administered during the other study visit. Participants will be blinded to the identity of kisspeptin or vehicle and the order of study visits will be randomised by an independent investigator (using Research Randomizer, [www.randomizer.org](http://www.randomizer.org)).

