On arrival, participants will change into loose hospital scrubs and lie supine for 30 minutes to relax. Female participants will have their urine tested at the beginning of each study visit to ensure that they are not pregnant. The participant will complete an MRI safety questionnaire on each visit before entering the MRI suite.

Blood samples will be taken at regular intervals through an intravenous cannula (not more frequently than 15 minute intervals) for measurement of LH, FSH, kisspeptin, testosterone, oestradiol, cortisol and oxytocin to ensure baseline reproductive hormone levels are equivalent between study visits and to observe any changes during each study. At least two clinically trained investigators will be present throughout each study visit. Participants will have their blood pressure recorded on arrival and on completion of the visit, with their pulse measured at regular intervals throughout MRI scanning.

At  $t = 0$  minutes, kisspeptin or vehicle will be administered (maximum administration time 105 minutes). At  $t = 30$  minutes, the fMRI scan will begin (maximum scan time 75 minutes). During fMRI scanning participants will be presented with standard, validated tasks designed to activate sensory, emotional, cognitive and reproductive brain structures so kisspeptin's modulation of this activity can be assessed.

i) Sensory Tasks

These may include olfactory tasks in which participants will be presented with validated odours in a randomised order. During the task, participants may be asked to state whether they can smell anything, and to rate the intensity and the pleasantness of the odour on visual analog scales which will be projected on a computer screen in the MRI scanner (20,21).

ii) Emotional Tasks

These may include facial perception tasks (22,23) and viewing of emotive images (7) to determine if changes in brain activity modulated by kisspeptin affect resultant behaviour.

iii) Cognitive Tasks

These may involve general mental capacity tasks, evaluating a range of basic sensory and cognitive modalities. A battery fMRI task (7) may be employed to assess visual, motor, auditory language and calculation functions; and N-back tasks may be used to assess working memory (24).

iv) Penile Tumescence Tasks (male participants)

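### The intranasal dose is capped by a per-minute rate with no delivery time, the scan is placed both after and within administration, and the visible text does not tie route or vehicle to a participant's two visits

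*Protocol*

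**What the plan says.** **Dose limits (Protocol, Kisspeptin).** The general limit names no route: "The dose of kisspeptin administered in this study will not exceed 0.72nmol/kg/min". The next limit is for one particular route and uses the same unit: "Similarly, the dose of intranasal kisspeptin will not exceed 0.72nmol/kg/min". The supporting experience is described as follows: "Kisspeptin has been given safely to over 500 male and female participants in intravenous and subcutaneous form without side effects". Duration has an upper limit only: "Kisspeptin and vehicle administration will not exceed 105 minutes duration".

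**Vehicle (same section).** "Vehicle administration will consist of gelofusine or normal saline". No rule says which fluid is used when.

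**Timing.** The Functional Brain MRI scan section says: "Maximum scan time per study visit will be 75 minutes, starting after administration of kisspeptin or vehicle". The fMRI Study Visits section says that at t = 0 "kisspeptin or vehicle will be administered (maximum administration time 105 minutes"), and that scanning begins at t = 30 minutes and lasts up to 75 minutes. The Secondary Outcomes section places the hormone and behavioural comparisons during administration.

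**Uniformity (fMRI Study Visits).** "all participants (groups A to F) will receive the same protocol (see figure 1) during each study visit". Figure 1 is not reproduced in the text at hand.

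**The concern.** The primary outcome is a within-person contrast of task-related BOLD activity, kisspeptin visit against vehicle visit. It has one clear meaning only if exposure during the scan is defined and the two visits differ in kisspeptin alone. Three parts of the text leave this open.

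- A rate limits an amount only when a duration goes with it. For intranasal administration no duration is given, so the limit does not say how much may be given as a discrete dose. The experience cited beside it does not include that route.
- Two sections place the scan differently relative to administration. The safety section says that kisspeptin clears quickly, so scanning during and scanning after administration need not be the same exposure. No half-life is given, so the difference cannot be sized from the protocol.
- Route and vehicle fluid are not tied to a participant's pair of visits. If fluid, volume, route or duration did differ between the two visits, that difference would be confounded with kisspeptin in a signal the protocol itself describes as reflecting blood flow. A larger sample would not remove it.

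**Working it through.** **1. What the rate limit bounds.** Inputs from the Kisspeptin section: 0.72 nmol/kg/min and a maximum of 105 minutes. For an administration lasting D minutes, the permitted total is 0.72 × D.

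- D = 30: 0.72 × 30 = 21.6 nmol/kg
- D = 105: 0.72 × 105 = 75.6 nmol/kg

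So the protocol does imply a ceiling of 75.6 nmol/kg. For a discrete intranasal dose D is not stated, and no narrower limit can be derived.

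**2. Scan against administration.** In the fMRI Study Visits section the scan runs from t = 30 to at most 30 + 75 = 105 minutes. If administration lasts D minutes (D ≤ 105) and the scan takes its full 75 minutes, the overlap is max(0, D − 30).

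| D (min) | Scan minutes inside administration, scan from t = 30 | Same, if the scan starts after administration ends |
|---|---|---|
| 30 | 0 | 0 |
| 45 | 15 | 0 |
| 60 | 30 | 0 |
| 105 | 75 | 0 |

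At D = 105 the literal reading of the Functional Brain MRI scan section puts the scan at t = 105 to 180, against t = 30 to 105 in the visit schedule. The two sections agree only if administration ends by t = 30, or if the first means after the start of administration.

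**3. Route and vehicle.** One limit names no route and another names the intranasal route. Intravenous and subcutaneous use appear only as past experience, and the cannula is described for blood sampling. Two vehicle fluids are allowed. Against this stands the statement that all groups receive the same protocol. Nothing visible assigns a route, fluid or duration to a group, participant or visit, and nothing says that they differ.

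**4. The sample size.** Inputs from Statistics and Data Analysis: means 0.74% and 0.48% (difference 0.26%), SDs 0.38% and 0.51%, correlation 0.40, alpha 0.05 (taken as two-sided), power 0.8.

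- SD of the difference = √(0.38² + 0.51² − 2 × 0.40 × 0.38 × 0.51) = √0.24946 = 0.4995
- Standardised difference = 0.26 / 0.4995 = 0.521
- Paired t-test: n = 31 gives power 0.801, n = 30 gives 0.787
- 31 / 0.90 = 34.4, rounded up to 35; 6 × 35 = 210

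The plan's figures reproduce. They rest on one amygdala effect from one previous study, and so on one common exposure.

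**5. Illustration only.** Suppose a share w of a group received a route whose effect is q times 0.26%. Neither w nor q is in the protocol. The mean difference becomes 0.26 × (1 − w + wq) and the variance 0.4995² + w(1 − w)(0.26 × (1 − q))². Power with 31 evaluable participants:

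| w | q = 1 | q = 0.75 | q = 0.5 | q = 0 |
|---|---|---|---|---|
| 0.25 | 0.80 | 0.75 | 0.68 | 0.54 |
| 0.50 | 0.80 | 0.69 | 0.55 | 0.27 |

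If the routes act equally, no power is lost.

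**The case against.** The timing conflict may be one of wording only. In the visit schedule 30 + 75 equals exactly 105, so the scan appears designed to end with the longest administration. The non-fMRI visits use the same clock for their tasks, and the secondary outcomes refer to the administration period. The conflicting phrase sits in a general description of MRI and may simply mean after administration has begun. This largely stands: the phrase needs correcting, but it is not evidence of two competing exposure plans.

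The rate limit is not empty either, because with the 105-minute maximum it gives a ceiling. That also stands. The ceiling does not, however, say what a discrete intranasal dose may contain.

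A reader might infer that routes are mixed within a group, or that a participant's vehicle differs from the fluid of their kisspeptin visit. The documents do not support either. The Kisspeptin section sets maxima and options. The visit section describes one protocol for everyone in a blinded crossover, and the figure it refers to may show the route and timeline. What remains is that the visible text does not state the matching on which the contrast depends.

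**Conclusion.** Two defects are in the text as written. The intranasal limit is in a unit that does not fix the amount of a discrete dose; the only total that follows is 75.6 nmol/kg over 105 minutes. The administration and scan clock is literally contradictory, by up to all 75 scan minutes when administration takes its maximum time. That size assumes the literal reading, and the contradiction disappears if the phrase means after the start.

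The open route and vehicle are a lesser matter: detail that the visible text does not supply, with a missing figure that may supply part of it. It would be tempting to conclude that the trial does not test one intervention and is underpowered. That does not follow. The sample size reproduces, and any power loss rests wholly on an assumed share and an assumed relative effect, with results from no loss to severe loss. This should be fixed, but no stated statistical figure is shown to be wrong.

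**What to change.** Reconcile the Kisspeptin, Functional Brain MRI scan, Secondary Outcomes and fMRI Study Visits sections:

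- Restate the intranasal limit in a unit that bounds the dose given. The value is for the clinical team to set, together with the experience that supports it for that route.
- Use one timeline for administration and scan in all sections and in figure 1.
- State that each participant's vehicle visit matches their kisspeptin visit in fluid, volume, route and duration.
- State the route or routes used. If there is more than one, report the routes separately in the primary contrast.

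The cost is amendment wording. If more than one route is used within a group, its 35 participants are divided between the routes, so each route's contrast is less precise than the sample size calculation assumes. Matching should be written down before visits take place, because a mismatch between visits cannot be corrected in the analysis.

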**Functional Brain MRI scan**

Magnetic resonance imaging (MRI) is a safe and established imaging technique, which has been used routinely in hospitals throughout the world for over 30 years. MRI does not involve the administration of radiation, and has no associated health risks. Functional MRI (fMRI) is a type of MRI that is used to determine which areas of the brain have greatest blood flow as a surrogate marker of brain function. fMRI uses blood oxygen level dependent (BOLD) analysis, which requires no contrast agent or drug administration. The MRI scanner contains a very strong magnetic field and individuals with any type of metal implanted in their body which could move in this field cannot undergo magnetic resonance imaging for safety reasons. This will be carefully checked for and such individuals excluded at the time of initial screening. MRI safety criteria will also be confirmed by MRI staff prior to each scan. In some circumstances, participants may attend for a pre-study acclimatisation visit during which they will undergo an anatomical brain MRI.

Participants will have the opportunity to watch a video about what to expect in the scanner at their screening visit. Participants lie supine in the scanner with their head placed in a padded head coil for support. At all times the participant will have access to an alarm button and will be able to verbally communicate with the investigator at the scanning console in-between scans. Maximum scan time per study visit will be 75 minutes, starting after administration of kisspeptin or vehicle. Participants will be able to communicate with the researchers throughout the scan and will receive reassurance as required.

All scans will be formally reported by a consultant neuroradiologist. Very rarely, abnormalities may be detected that warrant further investigation. In this situation the report would be communicated to the participant’s GP, who will arrange the appropriate specialist referral. A significant abnormality would lead to exclusion from further participation in the study.

**Participants**

Study participants will be recruited from print and online advertisements (including local and regional newspapers). Suitable participants will be allocated to the following groups:-

**Groups A and B:** Healthy males (A) and females (B).

**Group C and D:** Males (C) and females (D) with mild to moderate low mood defined by Patient Health Questionnaire 9 (PHQ9) scores between 5-15 (19).

**Group E and F:** Males (E) and females (F) with low sexual desire defined by Diagnostic and Statistical Manual of Mental Disorders (DSM) V criteria.

**Participant Consent and Safety**

Potential participants who respond to the study advertisements will be sent a participant information sheet and invited to attend a screening visit at our Clinical Research Facility at Hammersmith Hospital or St Mary's Hospital.

During the screening visit, full informed consent will be obtained before any medical assessment takes place. Participants will be informed that they are free to withdraw from the study at any time.

After consent has been given, suitability to enter the study will be assessed with a full medical history. All participants, including those with no past history of psychological and psychosexual disorders will be screened for these conditions with a careful psychosexual history and use of standardised, validated psychometric questionnaires (including PHQ9, GAD7, IIEF, SCI-M, SDI, SCOFF and DEBQ). Any new diagnoses that are made will be discussed with the participant by one of the study doctors and if the participant consents, their GP will be contacted to arrange ongoing management or specialist referral as appropriate. If participants still wish to take part in the study in spite of a new diagnosis of low mood or low sexual desire, then they will be offered a place in the relevant study group provided they meet all inclusion and exclusion criteria. Severe features of any mental health disorder e.g. PHQ9 score > 15 indicating severe depression, will be discussed urgently as appropriate with their GP or Imperial College Healthcare NHS Psychiatry Liaison team.

The screening visit will also involve a physical examination (including an ECG) and blood tests for sex hormone levels, metabolic parameters and to assess for any systemic illness. A urine pregnancy test will be conducted to exclude pregnancy in women of childbearing age.

